#### Missing Data

In the event of substantial missing data, data will be imputed using a multiple imputation procedure. The type of procedure (e.g., fully conditional specification, hot-decking, etc.) and the number of imputed data sets will be determined by the amount of missing data and the pattern of missingness. Efforts will be made to minimize loss-to-follow up; however, in the event that a patient's primary outcome (CLASS-3 score at the 1, 2, and 4-week follow ups) is unobtainable, we will (1) assume the worst and assign an “unfavorable” outcome for that patient in order to conduct the ITT analysis and (2) assume the best and assign a “favorable” outcome for that patient as a sensitivity analysis for the ITT analysis. These analyses will describe the boundary conditions for the models described above.

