### Data Analyses

#### Sample Size

Sample size calculations were conducted with the aim of achieving 80% power for the primary outcome. Computations were based on previous research using the Concussion Learning Assessment and School Survey, 3rd Ed. (CLASS-3) which reported on the mean, variability, and intercorrelations for metrics derived from the CLASS (47). The sample size was calculated for a 1:1 treatment allocation scheme with 80% power to detect an overall 20% difference in the mean of the CLASS-3 Academic Problems Scale at the two-sided α level of 0.05 (corresponding to a Cohen's ≈ 0.15). With these parameters, we will randomize 532 patients after assuming a loss-to-follow-up rate of 20%. Assuming minimal loss-to-follow-up, power is expected to be ~88%.

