#### Primary Outcome—CLASS-3 Academic Problems Scale

Analyses will be conducted under the intention-to-treat principle (ITT). Scores on the CLASS-3 Academic Problems scale (42 pt. scale) will be compared between intervention and control patients using a mixed-effects/multilevel linear regression. Experimental group and Timepoint (weeks 1, 2, and 4) will be included as independent variables. The mixed-effects model will be used in order to account for clustering within the data (e.g., clustering within provider, patient, etc.). When possible, the intercept and intervention slope will be included as random effects to evaluate the variability between providers and sites. Alternatives will be considered if model assumptions are not met or if the model fails to estimate properly.

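### Filling missing primary CLASS-3 scores with the same extreme value in both arms distorts the ITT estimate and does not bound the treatment difference, as the Missing Data section says it does

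*Protocol article*

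**What the plan says.** The section on the primary outcome adopts intention to treat and a continuous endpoint: "Scores on the CLASS-3 Academic Problems scale (42 pt. scale) will be compared between intervention and control patients", in a mixed-effects linear regression over weeks 1, 2 and 4.

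The Missing Data section gives two provisions. The general one is "In the event of substantial missing data, data will be imputed using a multiple imputation procedure", with the type of procedure left to depend on the amount and pattern of missingness. The specific one covers a patient whose CLASS-3 score at the week 1, 2 and 4 follow-ups is unobtainable. For that patient the study will (1) "assume the worst and assign an “unfavorable” outcome for that patient in order to conduct the ITT analysis" and (2) assign a favourable outcome as a sensitivity analysis. Neither clause mentions the treatment arm. The section closes: "These analyses will describe the boundary conditions for the models described above".

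The Participants/Setting and Sample Size sections plan 532 children, loss to follow-up held below 20%, and about 425 analysed.

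**The concern.** Clause (1) attaches the worst-case fill to carrying out the ITT analysis, and only clause (2) is called a sensitivity analysis. As worded, an extreme single imputation therefore enters the analysis on which the primary conclusion rests.

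Two consequences follow. First, a block of scores at the end of the scale shifts the mean of each arm by an amount that depends on how many children were lost there. It also adds variance unrelated to the intervention. Second, the closing sentence promises limits that the two analyses cannot supply. With similar loss in the arms, the two fills agree almost by construction. A reader told that worst-case and best-case assumptions gave the same answer would take that as robustness to missing data, although the assumption that matters (children lost from one arm differ from those lost from the other) was never varied.

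**Working it through.** **Inputs from the Sample Size and Participants/Setting sections.** Power and effect: "80% power to detect an overall 20% difference in the mean of the CLASS-3 Academic Problems Scale", "at the two-sided α level of 0.05"; 1:1 allocation; 532 recruited; 20% loss; 425 remaining; about 88% power with minimal loss.

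**The plan's own figures.** 425 / 0.80 = 531.25, rounded up to 532. For two means, 80% power with 212.5 per arm implies d = (1.960 + 0.842) × √(2/212.5) = 0.272. With 266 per arm, power = Φ(0.272 × √133 − 1.96) ≈ 0.88, which matches the stated figure. The stated effect size ("corresponding to a Cohen's ≈ 0.15") does not lead to 425 by this simple formula: d = 0.15 would need 698 per arm. The article refers to intercorrelations that it does not report. The SD below is therefore taken from d = 0.272. The bounding argument does not use it.

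**Bounding claim (no mean or SD needed).** Let δ be the control-minus-intervention difference among observed children, m the share filled in each arm, and v the common fill value.

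Estimated difference = (1 − m)δ + m(v − v) = (1 − m)δ, for any v.

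The worst and best fills coincide. The extremes of the difference come from opposite fills. On a 42-point range they are (1 − m)δ ± 42m.

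**Illustration.** Assumed: scale 0–42, higher = more problems, unfavourable = 42, favourable = 0, control mean 10, δ = 20% × 10 = 2, SD = 2/0.272 ≈ 7.4, no clustering, one score per child.

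- Both fills at m = 0.20: 0.8 × 2 = 1.6 points.
- True extremes at m = 0.20: 1.6 − 8.4 = −6.8 and 1.6 + 8.4 = +10.0.

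**Power under the worst fill.** Variance per arm = (1 − m)SD² + m(1 − m)(42 − mean)², with SD² ≈ 54.15, means of 10 (control) and 8 (intervention), and 266 per arm.

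| Share filled | Difference | Variance, control / intervention | SE | Power |
|---|---|---|---|---|
| 5% | 1.9 | 100.1 / 106.4 | 0.881 | 58% |
| 10% | 1.8 | 140.9 / 152.8 | 1.051 | 40% |
| 20% | 1.6 | 207.2 / 228.3 | 1.279 | 24% |

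The comparison is the plan's own 80% (20% lost) to 88% (almost none lost). The assumed control mean matters: at 20% filled, power is about 9%, 45% and 62% for control means of 5, 15 and 20. At 5% filled and a mean of 15 it is about 75%.

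**Unequal loss (control mean 10, δ = 2).** With shares m_C and m_I filled at 42, the difference is [10(1 − m_C) + 42m_C] − [8(1 − m_I) + 42m_I] = 2 + 32m_C − 34m_I.

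| Control / intervention filled | Worst fill | Best fill | True extremes |
|---|---|---|---|
| 20% / 20% | 1.6 | 1.6 | −6.8 to +10.0 |
| 25% / 15% | 4.9 | 0.7 | −5.6 to +11.2 |
| 15% / 25% | −1.7 | 2.5 | −8.0 to +8.8 |

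Setting the expression to zero at m_C = 0.20 gives m_I = 8.4/34 = 0.247, so about 5 percentage points more loss in the intervention arm cancels the effect.

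**The case against.** The best defence is that the two fills may be meant only to accompany the main model. The closing sentence covers both analyses and refers back to the models already described, which points to the mixed model as the headline result. Clause (1) pulls the other way by tying the fill to the ITT analysis, so this reading cannot be relied on. The bounding claim fails on either reading.

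Several stronger inferences are tempting, and the document does not support them:

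- *The rule dilutes the effect in general.* That holds for equal loss. With 25% control and 15% intervention loss the worst fill inflates 2.0 points to 4.9.
- *A fifth of the children will be filled.* The 20% is a ceiling on overall loss, and enrolled children are followed for up to 6 months. Read literally, the rule covers only children with no score at weeks 1, 2 and 4, so a child lost after week 1 would not be filled. The share may be well below 20%, hence the range in the table.
- *Multiple imputation and the extreme fill contradict each other.* The first may be meant for covariates, secondary outcomes and intermittent gaps, and the second for children with no primary score. What is unstated is which takes precedence.
- *The favourable and unfavourable categories are an error in themselves.* How they map to a 42-point score is an operational detail that an article may leave to the full protocol or SAP.
- *The power figures predict the trial's power.* Mean, SD and scale direction are assumed, and the planned model is longitudinal and clustered.

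**Conclusion.** The point stands as a fault in what the section states. Filling both arms with the same value cannot bound a between-arm difference. This follows from algebra and needs no assumption about the mean, the SD or the amount of loss. As worded, the worst-case fill also belongs to the ITT analysis of the primary outcome. There it attenuates the estimate by the factor (1 − m) under equal loss and biases it in either direction under unequal loss.

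The size is illustrative only and rests on the assumptions listed in the working. The loss of power ranges from moderate to severe with the share filled and the control mean. The sensitivity to a loss imbalance of about 5 percentage points is the more serious practical risk, because the primary result could then follow attrition rather than treatment. The text should be corrected before analysis.

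**What to change.** 1. State that the primary ITT analysis is the planned mixed model on all observed week 1, 2 and 4 scores under missing at random, with multiple imputation where needed, and that this takes precedence over any other missing-data rule.
2. Remove the worst-case fill from the ITT analysis.
3. Replace the two common fills, and the sentence about boundary conditions, with arm-opposed extreme fills (intervention worst with control best, and the reverse), a delta-adjusted tipping-point analysis, or both, labelled as sensitivity analyses.

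The cost is a change of wording and a few lines of analysis code. No further data are needed, and the sample size stays as it is.

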#### Multiple Testing

To the extent possible, we will track the number of analyses to report the false discovery rate, that is, the expected proportion of false positives. We will test the primary outcome variable at an α level of 0.05; for secondary outcomes, the false discovery rate will be formally controlled.

## Discussion

### Significance

The CDC has informative, evidence-based resources and existing instruments to support healthcare providers in the evaluation, management, and treatment of pediatric mTBI (https://www.cdc.gov/headsup/providers/index.html) (54). Although these resources are made available to all stakeholders and clinicians, the dissemination and implementation of intervention programs has not been rigorously evaluated in real-world settings, e.g., utilization and adoption across healthcare delivery systems (ED, UC, and PC). This study targets the public health concern and translational research gap in pediatric mTBI. We will use RE-AIM as a pragmatic model (44) to assist us in evaluating the implementation and effectiveness of a multi-component clinical intervention using clinician training, electronic clinical decision support, customized discharge instructions, and communication linkage tools to ultimately improve personalized diagnosis, management, and treatment of pediatric mTBI established from high-quality evidence.

### Public Health Impact

The *TEaM* Intervention's public health impact will be determined by healthcare provider reach and efficacy on the individual level and the implementation and adoption on the organizational level (35, 55, 56). We seek to carefully evaluate any translational and dissemination issues related to the application of the *TEaM* Intervention within real-world settings (43, 56), and believe this evaluation will provide further knowledge and inquiry for future studies, updates to evidence-based guideline recommendations and dissemination materials. Furthermore, evaluation of this intervention utilizing the RE-AIM framework (35, 55) is an appropriate method in determining the effectiveness and generalizability of the *TEaM* Intervention, providing the knowledge needed to inform our stakeholders (patients, parents, school personnel, providers and grant funders), and facilitate the translation of research into the clinical setting, thereby improving practice change, program sustainability and outcomes for children with mTBI.

### Contributions to the Field Statement

This study evaluates the impact of an evidence-based, multi-component pediatric mTBI intervention across multiple pediatric healthcare settings leveraging the eMR to facilitate clinical decision support and improve communication linkages since the release of the new CDC pediatric mTBI guidelines. Utilization of the RE-AIM framework (36) complemented with qualitative inquiry (RE-AIM QuEST) (38) to evaluate the impact of *TEaM* Intervention across multiple healthcare settings is a pragmatic approach in facilitating the translation of research into clinical practice.

The emphasis on HCP education, training, and communication linkage tools addresses the research priority in mTBI. Furthermore, this model evaluates the sustainability of the *TEaM* Intervention following the funding period through ongoing engagement and collaboration of stakeholders within the healthcare and school systems, community partners, and funding agencies. This knowledge may assist researchers, funders, and policymakers in identifying specific outcome measures, contextual factors and, clinician practices surrounding pediatric mTBI. The *TEaM* Program Logic Model (Figure 2) was inspired by and adapted from the work of Manca et al. (57) to assist in program planning. The logic model describes the inputs, outputs/activities defining each applicable dimension of the RE-AIM framework, projected short, intermediate, and, long-term outcomes of the *TEaM* Intervention. The *TEaM* Intervention has the potential to provide a nationally recognized evidence-based intervention developed and guided by the best available evidence, ultimately promoting usability, feasibility, and scalability across organizational settings. The program evaluation component of the *TEaM* Intervention may provide the knowledge needed to better understand the application of a multi-component, multi-setting intervention into the real-world and increase the uptake and dissemination of pediatric mTBI guidelines.

**Figure 2 F2:**
[figure not shown]
*TEaM* Logic Model inspired by and adapted from “Logic model for the BETTER 2 program” by Donna Patricia Manca et al. licensed under CC BY 4.0.

## Project Status

Study interventions requiring provider enrollment are in the development and refinement stages. Due to COVID-19, a delay within the study timeline has occurred as the investigative study staff as well as HCPs who will be randomized participating providers are Emergency Medicine providers or involved in programs that directly support that setting. This delay has impacted the expected timeline of provider recruitment. Similarly, patient presentations to the study sites initially decreased when distancing measures were first implemented in the United States (Figure 3). However, patient presentations have begun to return to pre-COVID-19 levels. Other project efforts such as publication and eMR/CDS refinement continue.

**Figure 3 F3:**
[figure not shown]
The number of patients screened per day at participating study sites. The red vertical line identifies March 11th, 2020 when the WHO declared the COVID-19 outbreak to be a pandemic. The black fit line was computed using smoothing splines. The λ parameter was set using generalized cross validation.

## Conclusion

Application of the RE-AIM framework (36) employing a mix-methods approach (RE-AIM QuEST) (38) is a model for evaluating the effectiveness of the *TEaM* Intervention to emphasize priorities of this public health concern surrounding pediatric mTBI. This evaluation method has the potential to provide the knowledge needed to critically appraise the impact of pediatric mTBI post- injury recovery interventions across multiple settings, enabling the uptake of best-available evidence within clinical practice.

## Ethics Statement

The study protocol was approved by the Institutional Review Board of Emory University (IRB Registration No. IRB00108674).

